### Compliance with ethical guidelines

#### Ethics committee.

All described studies and evaluations are performed with the approval of the responsible ethics committee, in accordance with national law, and in accordance with the Declaration of Helsinki of 1975 (in the current, revised version). For the process evaluation, a positive vote (No. 193/2020 of 15.10.2020) of the ethics committee of the University of Witten/Herdecke (Ethik-Kommission der Universität Witten/Herdecke) is available.

#### Data privacy.

Participation in the study is voluntary. All participants will be informed about the study in advance and will give their written consent. The consent to participate in the study can be revoked at any time and without disadvantages. The withdrawal can be made without giving reasons. The UW/H collects the quantitative and qualitative data pseudonymized (app survey) or anonymized (transcribed interviews). The interviews will be transcribed. Any information that could identify the interviewee will be deleted from the transcript. The provisions of confidentiality and the German Federal Data Protection Act (BDSG) are guaranteed.

### Study status

In May 2022, 2,581 pediatric practices registered with the BVKJ received the intervention materials. Since June 2022, participating pediatricians from the intervention group have been placing the signal stickers in the yellow examination booklets at regular examination and parents have been participating in the app survey. The article of the baseline survey of the BB3 intervention study shows that the socio-demographics of the parents-child pairs are similar to the population. In addition, significant correlations were found between high parental screen time and child development parameters [37]. Furthermore, the participation rate of pediatricians and demand for materials is high [38].

## Discussion

To our knowledge, this protocol describes the first process evaluations of an app-based study and complex intervention in outpatient pediatrics. The process evaluation combines two frameworks (RE-AIM and CFIR) and thus covers all aspects of the evaluation of the implementation process of a complex intervention. Implementation is multidimensional: first, structured parent education takes place in pediatric practices, then parents pass the intervention on to their children, which is why the process evaluation examines implementation outcomes and contextual factors at both levels. The quantitative and qualitative data will be collected in a multifaceted manner. The data collection will use methods before, during and two years after the start of the intervention study. The pre-intervention analysis is the baseline survey of parent-child pairs in the app survey. The short-term analysis will determine how well the intervention has started, as well as the participation rate of practices and parents. In addition, it is possible to see at the outset what problems there may have been with implementation in the pediatric practices or with the app survey. The medium-term analysis examines whether there is intervention fidelity and whether the project will be continued. The long-term analysis determines what experience pediatricians and parents have had with the BB3 intervention. The main study examines the screen use and development of children from 6 months to 3 years of age. The study collects participation rates and material orders. It also examined Maintenance until the end of the main study. We conduct the interviews of process evaluation spread over two years.

Interviews will identify extrinsic and intrinsic motivators that entice pediatricians and parents to participate in the BB3 intervention study. The qualitative content analysis should help to understand and explain the outcomes of the quantitative analysis using RE-AIM. The BVKJ is relevant to the profession and should therefore be a strong motivating factor for pediatricians to participate in the BB3 intervention study. Pediatricians exude a natural authority, which may persuade parents to implement the intervention. The materials are designed to provide parents with direct recommendations and support for using screen media and easy access to information. Parents are expected to take the risks seriously, show insight and understanding, and adapt their media behavior and that of their children.

The process evaluation uses RE-AIM and CFIR to determine how well the complex intervention is already implemented in pediatric practices and what actions still need to be taken to fully establish the intervention in outpatient pediatric care. The process evaluation will help understand how to implement a complex intervention in pediatric practices and how to reach parents for participation. The process evaluation will support the sustainability of the BB3 intervention and provide guidance for future complex interventions in pediatric health care research. Due to the novelty of digital research in outpatient pediatrics, this evaluation can be a basis for the development of future studies beyond the boundaries of pediatric health care research. Studies worldwide have shown that high screen media exposure in early childhood is associated with several health problems and developmental delays [2,5,13]. There are guidelines with recommendations on age-appropriate media times to reduce children’s screen time. The World Health Organization guidelines, recommend that children under the age of 2 should not spend any time on screens and children aged 2–4 should spend no more than 60 minutes a day [39]. The American Academy of Pediatrics (AAP) recommends no screen media exposure for children between 0 and 18 months [40]. In Germany, it is recommended to keep children away from screen media in the first 3 years of life [19]. Qualitative research has shown that parents are not well informed about guidelines on screen time for children [41,42]. The BB3 intervention mediates the recommendations of the German guideline. In the interviews, we will ask pediatricians and parents about their attitudes and acceptability towards the no screen till three recommendation. We will ask Pediatricians whether they agree with the recommendation and what they would change. We will evaluate whether parents can implement the recommendation or have difficulties. The process evaluation will examine whether pediatricians and parents find this, in comparison to other guidelines, strong screen limitation appropriate and feasible. The BB3 intervention study could promote the tightening of international WHO or other countries’ recommendations for screen time for infants and young children. This is possible in the case of proven effectiveness in the main study and approval and implementation of the recommendation by pediatricians and parents. In addition, the process evaluation will show how effectively parent education on screen time can be integrated into a routine examination in pediatric practices. Due to the cheap materials and easy implementation, the BB3 intervention will be applicable to other contexts with different healthcare systems. The materials can also be used in other areas, e.g., kindergartens and schools.

Intervention practices received a starter pack of materials containing a postcard by mail. To confirm participation, pediatric practices can stamp the postcard with their practice stamp and send it back to the sender. The number of returned postcards may differ from the actual participation rate, since sending the participation card is another effort. Employees in pediatric practices possibly save time and pediatricians start placing the signal sticker straight away. However, we can approximately determine the participation rate without a return postcard via repeat orders and general e-mail exchanges with the randomized practices.

In July 2022, one month after the start of the study, a telephone survey was conducted with randomized practices, including questions about the arrival of the starter pack, use of the materials and the practice’s initial assessment of the project. Most of the respondents are medical assistants. Especially in large practices, it can happen that a person is reached on the phone who is not involved in the BB3 study in their area of activity and does not know about it. As a result, the results of the telephone survey (participation, recommendation, etc.) may differ from the actual results. The data from the telephone survey serve to provide an overview of the arrival of the materials. Medical assistants accept the starter packs in most cases and pass them on to the pediatricians. In addition, pediatricians are difficult to reach for a survey. Therefore, it is useful to ask this questionnaire about the arrival of materials to medical assistants. We will generate more detailed information in the expert interviews.

A participation rate of parents can be determined via the app survey. This is done by assigning parents to their pediatric practice in the app. In this way, a local allocation of the participating parents can be made via the practice using the practice contact list. In the app survey, the second survey (U6) asks about the signal sticker in the yellow examination booklet. How many parents receive the signal stickers could be determined in real time using QR code tracking, which the QR code on signal stickers and waiting room posters does not yet have. However, conclusions about the number of signal stickers distributed can be drawn approximately from the number of stickers sent to pediatrician practices. An app survey can be a barrier for parents with lower income or limited digital literacy. In addition, not all pediatric practices in Germany use the app and distribute it to parents of patients. Both aspects can lead to a selection bias. To counteract this, we are collecting data as part of a sub-study “BLIKK Media” using a parent questionnaire in paper pencil, with a smaller sample size.

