### The intervention study

The process evaluation refers to the Germany-wide randomized controlled trial (Screen free till 3 abbr. BB3). BB3 is a complex intervention with routine parent education in pediatric practices to prevent active and passive screen media use by children under three years of age. In addition, there is an app-based longitudinal parent survey on screen time and child development. Pediatricians perform this intervention in practices during the regular examination of children aged about six months defined in the child guideline by the Federal Joint Committee of Germany [24]. These examinations check the general state of health and the age-appropriate development of children and adolescents.

First, all practices in the intervention group received a starter pack with the study materials (Return postcard, waiting room poster, 100 signal stickers) in May 2022. The practices participate in the study by self-selection.

Pediatricians find information about the study and the procedure in the study description. Further information and multiplier training is available on the project website.The intervention includes hanging the waiting room poster in the practice and distributing the signal stickers. The pediatricians stick the signal sticker in the children’s examination booklet. The main recommendations of BB3 are to engage the child without the use of screen media at least until the age of three; to enjoy meals free from screen media; to avoid screen media running in the background; and to avoid screen media use themselves in the presence of the child. The signal sticker sticks out like a bookmark and reminds parents of the project at least every time they visit the pediatrician.The project website provides scientific information, assistance in implementing the recommendations in the family environment and a parent newsletter with e-mail notification.

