**Implementation Process**		
Reach	absolute number, proportion and representativeness of participants in the app survey and of the use of the project website	app survey, website analysis
Effectiveness	impact of economic effects in practices, reduction of screen times and associated health problems	expert interviews, app survey
Adoption	absolute number, proportion, and representativeness of participating practices, interested institutions, settings of the persons involved	returned postcards, website analysis, expert interviews
Implementation	applicability of the intervention, fidelity (protocol-compliant implementation in practices), adaptations made to interventions and implementation strategies	telephone survey, documentary analysis, expert interviews, parent interviews
Maintenance	absolute number, proportion and representativeness of participating practices and parents after one year, extent to which the intervention becomes part of the routine organizational practices and guidelines	returned postcards, app survey, expert interviews, parent interviews

BB3: screen free till 3; RE-AIM: Reach, Effectiveness, Adoption, Implementation, Maintenance; CFIR: Consolidated Framework for Implementation Research.

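### Stickers sent to practices are only an upper bound on stickers given to parents, and the app survey, which asks parents about the sticker, is not a listed source for Implementation (fidelity)

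*Protocol article*

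**What the plan says.** On supply, the section on the intervention study reports that "all practices in the intervention group received a starter pack with the study materials (Return postcard, waiting room poster, 100 signal stickers) in May 2022" and that practices then decide for themselves whether to take part. The study status section gives the count: "In May 2022, 2,581 pediatric practices registered with the BVKJ received the intervention materials".

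On distribution, the Discussion notes that the QR code on stickers and posters does not yet allow tracking, and then proposes that "conclusions about the number of signal stickers distributed can be drawn approximately from the number of stickers sent to pediatrician practices". Shortly before, the same paragraph says that "the second survey (U6) asks about the signal sticker in the yellow examination booklet", and that the app assigns parents to their practice.

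On fidelity, the Implementation row of Table 1 includes protocol-compliant delivery in practices. Its sources are "telephone survey, documentary analysis, expert interviews, parent interviews". The app survey is listed for Reach, Effectiveness and Maintenance, but not for Implementation.

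On the telephone survey, the methods list implementation among its topics, and the Discussion says that it covered use of the materials as well as their arrival. The Discussion adds that most respondents were medical assistants, that answers may depart from what actually happened, and that "The data from the telephone survey serve to provide an overview of the arrival of the materials".

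**The concern.** A process evaluation has to say how much of the intervention reached families. If the main trial shows no effect, the first question will be whether the intervention failed or was not delivered. A count of stickers that left the sender cannot answer this, because most or all of that count may have been fixed by the mailing and not by anything the practices did.

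The article describes a better measure and does not assign it to the construct that needs it. The U6 question is put to parents at about one year of age, after the six-month examination at which the sticker is placed, and each answer can be traced to a practice. Without it, the Implementation row has no source that can give a usable estimate of the proportion of families who received the sticker.

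**Working it through.** The article states no distribution or fidelity figure, so there is nothing to reproduce. The check has three parts.

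**1. What the sticker count can show**

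Inputs: 2,581 intervention practices (recruitment and study status sections) and 100 stickers per starter pack (section on the intervention study).

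Starter stickers sent = 2,581 x 100 = 258,100.

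Starter stickers given out = 258,100 x p x u, where p is the share of practices taking part and u the share of the pack they use. Neither p nor u is given in the article. Sent stickers do not depend on p or u.

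| Assumed p | Assumed u | Given out | Share of those sent | Sent / given out |
|---|---|---|---|---|
| 20% | 25% | 12,905 | 5% | 20 |
| 30% | 100% | 77,430 | 30% | 3.3 |
| 50% | 100% | 129,050 | 50% | 2.0 |
| 70% | 100% | 180,670 | 70% | 1.4 |
| 100% | 100% | 258,100 | 100% | 1.0 |

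The error can run in one direction only, and its size is set by uptake, which is what the evaluation wants to learn. These rows cover the starter mailing alone. With R re-ordered stickers, all used, the ratio becomes (258,100 + R) / (258,100 x p x u + R). This is nearer to 1 for any positive R when p x u is below 1, so re-orders reduce the overstatement without removing it.

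**2. What the listed Implementation sources can show**

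- Telephone survey: 800 / 2,581 = 31.0% of intervention practices. It was done in July 2022, one month after start, and is complete. It asked about use, but mostly of medical assistants. The Discussion assigns fidelity to the medium-term analysis, which a call at one month cannot serve.
- Interviews: around 15 pediatricians and 20 parents, sampled for heterogeneity and deliberately including practices not actively participating and parents without the sticker. Even if they were random samples, the exact (Clopper-Pearson) 95% intervals would be 27% to 73% for 10 of 20 and 27% to 79% for 8 of 15.
- Documentary analysis: not defined further. If it means the practice documentation in Table 2, it holds items such as postcards, re-orders, questions and feedback, none of which records a sticker handed to a parent.

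**3. What the U6 item could show**

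The number of U6 respondents is not given. For an assumed sticker share of 50%, the 95% half-width is 1.96 x sqrt(0.25 x D / n), where D is the design effect for clustering by practice.

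| Assumed n (intervention practices) | D = 1 | D = 2 (assumed) |
|---|---|---|
| 500 | 4.4 points | 6.2 points |
| 1,000 | 3.1 points | 4.4 points |
| 2,000 | 2.2 points | 3.1 points |

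Over this range, sampling error would be small enough for the estimate to be useful. Selection into app use would remain the main weakness.

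**The case against.** The strongest reply is that the criticised sentence stands among the limitations, is hedged as approximate and follows an admission that tracking is not available. Stickers sent are not named as a source in the Implementation row, and no analysis in the article equates them with fidelity. The U6 item is openly mentioned, so the data are planned, and the gap amounts to one missing entry in a table. This is largely right, and it is why the point is not graded higher. The hedge does not fully answer it, however: an approximation suggests error on both sides, whereas this count can only be too high.

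Some stronger readings are tempting and should not be adopted.

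- A reader might infer that none of the sources measures delivery. The telephone survey did ask about use and implementation. It is an early, second-hand measure, not the absence of one.
- A reader might take re-orders and e-mails as a further faulty measure of delivery. The article says "we can approximately determine the participation rate without a return postcard via repeat orders and general e-mail exchanges with the randomized practices". That concerns practice participation, which is Adoption in Table 1. Nothing says that e-mails are counted regardless of content.
- A reader might see the absence of the sticker question from Table 2 as evidence that it will not be analysed. The app row there also omits screen times and developmental parameters, which the app is said to collect. The table is not exhaustive, and the absence shows little.
- A reader might quote the 1.4- to 3.3-fold overstatement as a property of the trial. It rests on assumed uptake with all-or-none use of the pack.

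**Conclusion.** The point holds in a narrow form. Stickers sent measure supply; as a figure for distribution they are an upper bound, of which 258,100 is fixed by the starter mailing whatever the uptake. The only direct quantitative measure of receipt that the article describes is not assigned to Implementation, and the sources that are listed there cannot estimate a delivery proportion well.

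The size of any overstatement cannot be fixed from the article, because uptake, pack use and re-order volume are not given. The conclusion itself needs none of these. It rests on the unconditional mailing, on self-selection afterwards, and on the content of the Implementation row. Severity: should-fix.

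**What to change.** 1. Add the app survey (U6 sticker item) to the sources in the Implementation row of Table 1.
2. Report the proportion of U6 respondents in intervention practices who report the sticker, overall and by practice, with confidence intervals that allow for clustering by practice.
3. Report stickers sent only as an upper bound, with the starter mailing and re-orders shown separately.
4. Optionally, use a U6 sticker report as additional evidence that a practice takes part where no postcard came back.

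The cost is a table entry, a change of label and a tabulation of data that the app already collects. Two limits should be stated with the result. The item covers app users only, a selection bias that the Discussion acknowledges. It also records the sticker and not the counselling, so it measures one component of fidelity. The article says that the paper questionnaire of the sub-study is identical to the app questionnaire; if it carries the sticker question, it could serve as a small check on the first limit.
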